#### Evaluation of the HEAL-D intervention

Process evaluation is an essential part of testing complex interventions^45^ and will be used in our feasibility trial to evaluate the HEAL-D intervention and the feasibility of trial procedures. Our process evaluation aims to achieve the following:Test the intervention theory and whether the mechanisms of change operationalise as hypothesised.Understand how the multiple components of the intervention interact.Evaluate contextual factors that influence operationalisation of the intervention’s theory/mechanisms of change and any unintended effects of these factors.Evaluate whether the intervention is differentiable from ‘usual practice’.Evaluate implementation of the intervention, particularly ‘reach’ (eg, who receives the intervention), ‘dose’ and completion rates, and intervention fidelity (eg, coverage of core materials and learning objectives during delivery, and the extent to which the programme is delivered in accordance with the delivery manual, what adaptations are undertaken and why).Evaluate acceptability of the intervention to patients, healthcare professionals and commissioners.Evaluate intervention embedding and sustainability, for example, what are the barriers and facilitators to the uptake of the intervention in current care pathways.

A range of quantitative and qualitative data will be collected, as detailed in table 1. Attendance records, observation checklists, session/programme evaluation forms completed by patients and records of session activities completed by educators will provide quantitative data and will be used to evaluate a number of process domains, as indicated in table 1. Our process evaluation will mainly focus on qualitative evaluations, with which we will use inductive reasoning to determine whether the intervention requires further development and adaptation. Patient interviews and focus groups, and interviews with educators, healthcare professionals and commissioners, and session observation notes will provide qualitative data for the evaluation of a number of process domains, as detailed in table 1.

**Table 1 T1:** Mapping of the HEAL-D feasibility study research questions, process evaluation data sources and evaluation methods

Process evaluation domain and research questions	Data sources										Evaluation method
	Patient questionnaires	Session observations	Session record of activities	Patient evaluation forms	Educator interviews	Patient interviews	Patient focus groups	Attendance records	HCP interviews	Commissioner interviews	
Testing intervention theory and mechanisms of change											
Are the intervention’s mechanisms of change operationalised as hypothesised?	X	X	X	X	X	X	X				Qualitative data collected through interviews/focus groups with patients and educators, and session observation notes will be used to evaluate how the theory of the intervention operationalises and interacts with contextual factors.
How is the operationalisation of the mechanisms of change influenced by contextual factors?		X	X		X	X	X				
Does the interaction of the mechanisms of change with contextual factors give rise to unintended effects?		X	X		X	X	X				
Assessing usual practice and contamination											
Is HEAL-D differentiable from ‘usual practice’?						X					Interviews will be conducted with patients from both arms. Experiences of the intervention and control will be explored. With control patients issues of contamination and perceptions of ‘usual care’ will be discussed.
Is there contamination in control patients?						X					
Assessing implementation											
What is the intervention reach and dose?	X							X			Questionnaire data will assess who receives the intervention and how representative they are, for example, age, gender, ethnicity and working status. Attendance records will be used to quantify the proportion of patients receiving the full versus part intervention.
Are the HEAL-D components/sessions delivered with fidelity and what is the nature of any adaptions?		X	X		X						To assess fidelity and compare intervention deliveries and contextual impacts educators will complete a record of activities and materials and list any resources/activities/discussions that were additional to the standardised schedule. These will be explored in depth in educator interviews that will be conducted at the end of the programme delivery. The research team will observe HEAL-D delivery to quantitatively assess coverage of curriculum, use of supporting materials and behaviour change techniques, quality of delivery and participant engagement (binary score or a 5-point Likert scale). Observers will qualitatively document course adaptations and general contextual observations.
Does the delivery of HEAL-D differ between sites, and what gives rise to differences?		X	X		X						
How well are the HEAL-D components/sessions delivered?		X	X								
Assessing intervention acceptability											
Is HEAL-D acceptable to patients, commissioners and healthcare professionals?		X		X		X	X		X	X	Acceptability will be evaluated through a range of qualitative and quantitative data. Quantitative data will be generated in patient evaluations, which will use 10-point scales to assess their views on the quality of the programme content, structure, format and delivery; the sessions/programme will be deemed ‘acceptable’ where they score ≥6 points. Interviews/focus groups with patients, educators, healthcare professionals and commissioners will explore acceptability through qualitative data, for example, reasons for attendance/non-attendance among patients and suggestions for amendments.
Assessing intervention sustainability											
How likely is the HEAL-D intervention to be sustainable and what factors might ensure sustainability?									X	X	Qualitative data collected through interviews with healthcare professionals and commissioners will be used to evaluate barriers and facilitators to implementation of HEAL-D into current care pathways, and its fit with organisational priorities, and the feasibility of sustained resource allocation to the HEAL-D intervention if found to be successful.

HCP, healthcare professionals; HEAL-D, Healthy Eating & Active Lifestyles for Diabetes.

#### Evaluation of trial procedures

The feasibility of trial procedures will be evaluated, particularly rates and methods of recruitment, retention, completion, contamination between study arms and the proposed data collection methods:

##### Recruitment

Several different pathways of recruitment will be implemented, for example, screening of primary care databases and letters of invitation, face-to-face referral during medical appointments, self-referral via posters and word-of-mouth referral. We will assess uptake rates from these different pathways to enable us to identify the most effective methods and assess the feasibility of recruiting for a full-scale trial.

##### Retention and completion

We will assess the rate of retention both within the HEAL-D intervention (ie, numbers completing each session and the full programme) and the feasibility trial (ie, numbers completing baseline and endpoint assessment visits). We will evaluate the feasibility of randomising and retaining a control arm by assessing dropout rates and comparing these between the study arms; we will also interview control arm patients to explore the acceptability of being assigned to the control arm.

##### Data collection methods

We will assess the frequency of missing data and any trends in which data is missing, for example, self-complete questionnaires, blood measures, to assess the feasibility of our data collection methods.

##### Contamination

We will interview patients from the control arm to explore issues of contamination, for example, did their participation in the trial promote change in self-management behaviours or motivate information-seeking behaviours, did they know anybody in the intervention arm or discuss the intervention with anybody.

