### Phase 2: evaluation of HEAL-D; a culturally tailored T2D self-management programme for African and Caribbean communities

In phase 2, a feasibility study, with an embedded process evaluation, will be conducted to address the following objectives:Evaluate the HEAL-D intervention, particularly its theoretical under-pinning, acceptability, fidelity, issues of implementation and sustainability.Evaluate the feasibility of trial procedures, considering issues such as rates of recruitment, retention, completion and contamination.Estimate the effect size of potential trial outcomes including HbA1c, weight, waist circumference, blood pressure, dietary intake, physical activity levels, diabetes knowledge and quality of life, to inform an effectiveness trial.

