### Study design

The feasibility study will use a randomised controlled design, with individual patients as the unit of randomisation, evaluating HEAL-D against usual care. In addition, there will be a cohort of phase 1 codesign patients who will be allocated to the intervention arm (not randomised) because their involvement in the intervention design phase would contaminate the control arm. These patients will be included in the feasibility study to enable us to evaluate the impact of former involvement on intervention engagement, acceptability and ownership.

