### Intervention and control arms

Participants in the control arm will continue with usual care deemed appropriate and delivered by their primary care team, which may include referral to group structured education and/or one-to-one consultations with healthcare professionals.

Participants in the intervention arm will be offered the HEAL-D programme, which will deliver a curriculum of culturally tailored, evidence-based diet and physical activity education and behaviour change in a group setting. In line with clinical guidelines, the programme will be delivered by trained educators (external to the research team); favoured educators (eg, lay educators vs healthcare professionals) will be identified in the codesign process. The details of each session, particularly the behaviour change techniques and corresponding activities/materials, will be identified through the codesign work.

The proposed curriculum will map to evidence-based guidelines and will be as follows:An introduction to T2D self-management principles.Physical activity in T2D management.Carbohydrates and portion sizes.Weight management for T2D.Managing cardiovascular health.

In line with clinical guidelines for diabetes structured education, the education sessions will be delivered through educator-led interactive discussion; however, support materials will be provided to reinforce the learning, detailing evidence-based diet and physical activity guidance, which is culturally tailored for the African and Caribbean communities.

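### Contamination is named among the rates to be evaluated, but the plan gives it only exploratory interviews, with no definition and no denominator

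*Protocol article*

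**What the plan says.** All references are to the protocol article; no SAP was available.

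- **Phase 2 objectives.** The second objective is to judge the feasibility of trial procedures, "considering issues such as rates of recruitment, retention, completion and contamination".
- **Evaluation of trial procedures.** The lead sentence returns to the topic: "particularly rates and methods of recruitment, retention, completion, contamination between study arms and the proposed data collection methods".
- **Contamination.** The method is: "We will interview patients from the control arm to explore issues of contamination". The example prompts cover whether trial participation changed behaviour or led to information seeking, whether the control knew anyone in the intervention arm, and whether the intervention was discussed with anybody.
- **Table 1, usual practice and contamination.** Both rows carry one mark, under patient interviews; the patient questionnaire column is empty. The method column says: "With control patients issues of contamination and perceptions of ‘usual care’ will be discussed".
- **Evaluation of the HEAL-D intervention.** The general approach is stated: "Our process evaluation will mainly focus on qualitative evaluations, with which we will use inductive reasoning".
- **Study design.** The trial is randomised "with individual patients as the unit of randomisation, evaluating HEAL-D against usual care". The codesign patients are placed in the intervention arm without randomisation because they would otherwise contaminate the control arm.
- **Intervention and control arms.** Usual care is variable, "which may include referral to group structured education and/or one-to-one consultations with healthcare professionals".

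**The concern.** A rate needs a definition of the event, a count and a denominator. For contamination the article gives none of these. The neighbouring procedures are counted: dropout is compared between arms, completion of sessions and visits is tallied, and the frequency of missing data is assessed. Contamination stands in the same list of rates but has no count.

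The design makes the question a real one. Individuals are randomised to a group programme, word of mouth is one of the recruitment routes, and the sponsor already regards contamination as serious enough to keep the codesign cohort out of randomisation. If controls take up HEAL-D content, the difference between arms shrinks. A later trial planned without any figure for this may be too small.

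**Working it through.** **1. Objective against method.**

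| Item in the list of rates | What the article plans |
|---|---|
| Recruitment | Uptake rates by pathway |
| Retention and completion | Numbers completing sessions, the programme and assessment visits; dropout compared between arms |
| Contamination | Interviews with control patients to explore issues; Table 1 marks patient interviews only |

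Only the last row has no count. Table 1 exists to map each question to its data sources, so this is a stated method that falls short of a stated objective. It is not a detail that the article merely left out.

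**2. How many controls could be asked.** From Participants: 40 + 40 randomised plus 40 not randomised = 120, which reproduces the stated total. The stated 20% dropout, if it applies equally to the control arm, leaves 40 × 0.8 = 32 controls at follow-up.

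**3. Precision if no contamination is reported.** The upper end of the two-sided exact 95% CI for 0/n is 1 − 0.025^(1/n). The article does not state the number of controls interviewed, so a range is shown; every n below 32 is an assumption.

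| Controls asked | Upper limit for 0/n |
|---|---|
| 8 | 37% |
| 10 | 31% |
| 20 | 17% |
| 32 | 11% |
| 40 | 9% |

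**4. Precision if some is reported.** Wilson 95% CI for x/n with z = 1.96: [p + z²/2n ± z√(p(1−p)/n + z²/4n²)] / (1 + z²/n). For 6/32, p = 0.1875:

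- centre term: 0.1875 + 0.0600 = 0.2475
- half-width term: 1.96 × √(0.00476 + 0.00094) = 0.1480
- divisor: 1.1200
- interval: 0.0996/1.1200 = 8.9% to 0.3955/1.1200 = 35.3%

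By the same formula, 3/32 gives 3% to 24% and 10/32 gives 18% to 49%.

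**5. What dilution could cost.** Suppose a share c of controls receives the full HEAL-D effect and the rest none. The difference between arms is then multiplied by (1 − c), and the required sample size by 1/(1 − c)²:

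- c = 10%: 1/0.81 = 1.23
- c = 20%: 1/0.64 = 1.56
- c = 30%: 1/0.49 = 2.04

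This is a worst case. A control who talks with a participant or sees a leaflet is unlikely to gain what a participant in the group programme gains.

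**The case against.** The strongest reply is that the qualitative approach is deliberate. The process evaluation is declared mainly qualitative, Table 1 asks whether contamination occurs and not how often, and the sentence under Evaluation of trial procedures is too loose to make every item in it a rate, since it ends with data collection methods. On that view the phase 2 objective is merely worded carelessly. This has weight against the second sentence but not against the objective itself, where the word for rates governs all four items. Rewording the objective would remove the mismatch, but the trial would then lose a figure it could have for very little.

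A second reply also stands in part. Two of the interview prompts, on knowing someone in the intervention arm and on discussing the intervention, can be answered yes or no. Put to every control in the same form, they would give a crude proportion. So a rate is not beyond this trial's reach; the plan simply does not commit to obtaining one.

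A third reply is that diet, physical activity and diabetes knowledge are measured in both arms. That may show change among controls, but it cannot tell whether HEAL-D caused it.

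A reader might go further in three ways that the article does not support:

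- *The rate is needed to choose between individual and cluster randomisation.* Cluster randomisation is never mentioned. The article says only that its estimates should inform the best design of a full-scale trial.
- *Only a subset of controls will be interviewed.* The number is not given, and a full protocol may state it.
- *Uptake of usual-care education is also a promised rate left unmeasured.* No such rate is promised. Table 1 asks whether HEAL-D can be told apart from usual practice, and for that "Experiences of the intervention and control will be explored".

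**Conclusion.** The point holds in a limited form. The objective names a contamination rate; the stated method is exploratory interviewing with no definition of a contaminated control and no denominator. As written, the plan does not produce that rate.

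The gain from repair is useful but modest. With about 32 control completers (20% dropout in the control arm assumed), the trial could exclude contamination above about 11% if none were reported. With 6/32 reported, the interval of about 9% to 35% would correspond to worst-case inflation of roughly 1.2 to 2.4 (1/0.911² to 1/0.647²). That is enough to distinguish a negligible problem from a large one, but not to fix a dilution allowance precisely. The inflation factors rest on full transfer of the effect to contaminated controls and should be read as upper bounds.

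**What to change.** At the existing 26–32-week visit, after the outcome measures, put short closed questions to every control:

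1. Did you discuss the content of HEAL-D with someone taking part in it?
2. Did you see or use HEAL-D materials?
3. Do you know someone taking part in HEAL-D? Record this as opportunity for contact only.

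Define contamination in advance as a yes to question 1 or 2. Report the number answering, the proportion and its 95% CI, with the interval method named beforehand. Keep the interviews to explain how contact arose and what it changed. Mark the questionnaire column in the contamination row of Table 1.

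Optionally, ask both arms whether they attended any other structured diabetes education since baseline, and report this by arm. It would support Table 1's question about usual practice, but it is an addition and not the repair of an unmet promise.

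The cost is three or four items at a visit already planned, and a minor amendment. The drawbacks are slight extra burden and the chance that the questions prompt controls to seek out HEAL-D content. Asking them last limits this. The article does not say whether the three-day accelerometer wear follows the visit; if it does, ask the items when the device is returned.

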### Patient and public involvement

Service user involvement is intrinsic to this proposed research, which uses participatory methods to engage patients and other stakeholders in the intervention design. The protocol provides extensive detail of how patients will be involved in the design, recruitment, conduct and dissemination of the research.

### Ethics and dissemination

All data will be anonymised and data protection protocols followed.

The study findings will be disseminated to the scientific community via conference presentations and peer-reviewed manuscripts and to healthcare professionals via national and local clinical networks. The findings of the study will be communicated to our participants and local communities via the community networks and figureheads who we will engage in our participatory methods; we will give presentations at church events and publish a newsletter via our study website (www.heal-d.co.uk).

## Discussion

This paper presents the protocol for the design and feasibility testing of HEAL-D, a culturally tailored T2D self-management programme for UK African and Caribbean communities. This study will employ rigorous complex intervention methodology to develop and evaluate the implementation of a culturally tailored T2D self-management intervention. The intervention’s curriculum will be based on existing evidence-based guidelines for diet and lifestyle management of T2D; participatory codesign methods will be employed to foster community engagement and partnership. We will use a ‘bottom-up’ approach to identify the cultural adaptations of our intervention and identify its theoretical basis through thematic analysis and the COM-B change framework. The feasibility study will provide us with key information about the feasibility of running a full-scale trial of HEAL-D, and process evaluation methods will enable us to understand how and why the intervention is effective or ineffective.

To date there have been no tailored education programmes for black British communities. Indeed, it is not known to what extent culturally tailored care is needed for black British communities as little work has been undertaken with these communities. Our codesign work is intended to explore the sociocultural barriers and facilitators to behaviour change and structure HEAL-D accordingly. We acknowledge that we are likely to find huge diversity within our black British communities and *culture* will likely be only one of many important factors that affects their health behaviours. However, our codesign work will provide a more comprehensive theoretical underpinning for the content of our programme than that which currently exists and will provide us with a framework on which to evaluate the effectiveness of our programme. This work will provide essential information and evaluation to inform the design of a future definitive trial.
